### Secondary Outcomes

The secondary outcomes assessed in this study will include the following:

Stability of the advanced or transported segment: evaluated by bidigital palpation and CBCT and graded on a 5-point bone stability scale (1=highly unstable; 5=highly stable).Soft tissue healing: evaluated by the Landry wound healing scale at all times of follow-up and graded from 1 (very poor) to 5 (excellent).

All outcome assessments will be performed by evaluators who are blinded to the treatment group. CBCT scans will be anonymized, coded, and randomized before analysis. In cases where unblinding may occur (eg, visible hardware on radiographs), a second independent blinded reviewer will reassess.

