### Intervention Delivery

All surgeries will be performed by experienced oral and maxillofacial surgeons under general anesthesia.

The surgical procedures for both study groups will be standardized and carried out according to established protocols, as outlined below:

In *group A (dentoalveolar transport distraction)*, after adequate orthodontic preparation and osteotomy, a custom-fabricated intraoral distractor was placed. Distraction commenced after a latency period of 5 to 7 days, at a rate of 1 mm per day until gap closure, followed by a consolidation period of 8 to 12 weeks.In *group B (unilateral Le Fort I advancement)*, standard Le Fort I and palatal osteotomies were performed. The cleft-side maxillary segment was repositioned medially and stabilized using a surgical splint and titanium plates.

Postoperative care will be standardized across both groups and included antibiotics, analgesics, antiseptic rinses, and dietary modifications.

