### Outcome Measures and Data Collection

Data collection will occur at predefined intervals: preoperatively; immediately after surgery; and at 1, 3, 6, and 12 months of follow-up.

The following outcome variables will be systematically evaluated in both groups:

Alveolar gap closure will be measured radiographically using cone beam computed tomography (CBCT) at each interval.Maxillary arch form will be classified (U-shaped, V-shaped, or asymmetrical) using dental models and occlusal views.Segment stability will be assessed clinically and via CBCT using the 5-point bone stability scale.Soft tissue healing will be evaluated by blinded assessors using the Landry wound healing scale.

All CBCT images will be anonymized and randomized. Two independent evaluators, blinded to group assignment, will perform measurements. If visible hardware reveals the treatment allocation, a second reviewer re-evaluated the image independently.

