### Postoperative Care

All patients will receive antibiotics, analgesics, chlorhexidine mouth rinses, and dietary instructions. Follow-up visits will be scheduled at 1 month, 3 months, 6 months, and 1 year postoperatively.

As this is a prospective observational study, treatment allocation is not randomized. Patients are assigned to either the dentoalveolar transport distraction group or the unilateral Le Fort I advancement group based on specific clinical indications determined by the treating maxillofacial surgeon. Criteria such as cleft morphology, cleft width, presence of adequate bone stock for distraction, soft tissue quality, and anticipated compliance with the distraction protocols are considered during group assignment. To minimize selection bias, all assessments are conducted using standardized protocols, and outcome evaluators are blinded to the intervention type. Additionally, baseline characteristics of both groups will be statistically compared to assess equivalency, and any confounders will be adjusted for during analysis using multivariate regression techniques.

To further minimize allocation bias inherent to the nonrandomized design, we will perform stratified enrollment based on cleft width and age groups. Additionally, a propensity score adjustment will be conducted in the final analysis to balance any observed confounders between groups.

Missing data may arise from loss to follow-up or incomplete clinical or radiographic records. These will be assessed for randomness using the Little missing completely at random test. If data are missing at random, multiple imputation using chained equations will be applied to minimize bias. Variables with >20% missing data will be excluded from the primary analysis but may be used in sensitivity analysis. Potential confounders, such as patient age, cleft width at baseline, and compliance with treatment protocols, will be identified a priori based on clinical relevance and literature review. These variables will be included in multivariate regression models (eg, linear regression for continuous outcomes such as gap width and logistic regression for binary outcomes such as successful closure) to adjust the primary effect estimates. Adjusted effect sizes and CIs will be reported alongside unadjusted comparisons.

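### A second reader of the same image cannot undo unblinding by visible hardware, and the claim that all assessments are blinded fails for in-mouth examination while appliances are in place

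*Protocol article*

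**What the plan says.** The blinding claim in Secondary Outcomes has no exceptions: "All outcome assessments will be performed by evaluators who are blinded to the treatment group". For images, the same section adds that "CBCT scans will be anonymized, coded, and randomized before analysis".

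Two sections foresee that hardware may reveal the group. Secondary Outcomes says: "In cases where unblinding may occur (eg, visible hardware on radiographs), a second independent blinded reviewer will reassess". Outcome Measures and Data Collection says: "If visible hardware reveals the treatment allocation, a second reviewer re-evaluated the image independently". The latter section already plans two independent blinded evaluators for the CBCT measurements.

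The hardware differs between the groups. Group A receives a custom intraoral distractor. In group B the segment is "stabilized using a surgical splint and titanium plates" (Intervention Delivery).

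Stability is "evaluated by bidigital palpation and CBCT and graded on a 5-point bone stability scale" (Secondary Outcomes). Gap closure, a primary outcome, is measured clinically as well as by CBCT (Primary Outcome).

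Postoperative Care then offers blinding as a safeguard against a different problem: "To minimize selection bias, all assessments are conducted using standardized protocols, and outcome evaluators are blinded to the intervention type".

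**The concern.** Blinded assessment protects against detection bias only if the assessor cannot tell the groups apart. The plan recognises that hardware can reveal the group, but its remedy changes the reader and leaves the cue in place. For palpation and clinical gap measurement it describes no remedy, because the hardware rule covers images only.

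Part of what is measured depends on judgement: the stability grade is an ordinal score, and arch form is a classification. The groups are very small (7 planned per group; 7 and 5 enrolled as of June 2025). Allocation is by the treating surgeon, so assessment bias would add to confounding. As written, the report would present detection bias as controlled for all outcomes when for some outcomes and visits it is not.

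The sentence in Postoperative Care compounds this. Selection bias here comes from how patients are assigned to a technique. Blinding the person who later measures the outcome does not affect that.

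**Working it through.** The plan gives no figure for this point, so there is none to reproduce. The check compares sections and makes one timing calculation.

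**Step 1: does the re-read restore blinding?** Anonymizing, coding and randomizing scans hides identity and order. None of these steps removes metal from the image. The second reviewer re-evaluates the same image, so the cue is still there. A second reading can improve reliability, but two evaluators are already planned for that purpose. The re-read rule therefore does nothing for blinding.

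**Step 2: when is the distractor in the mouth?** Inputs from the protocol article:

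- latency 5 to 7 days, distraction at 1 mm per day, consolidation 8 to 12 weeks, that is 56 to 84 days (The Dentoalveolar Transport Distraction Group);
- cleft width 1.0 to 2.1 cm, mean 1.5 cm, that is 10 to 21 mm, mean 15 mm (Results; both groups combined);
- visits immediately after surgery and at 1, 3, 6 and 12 months (Outcome Measures and Data Collection).

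Assumptions: the distance distracted equals the cleft width, and the distractor stays in place through consolidation. The document does not state when it is removed.

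End of consolidation = latency + width in mm ÷ 1 mm per day + consolidation:

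- shortest: 5 + 10 + 56 = day 71;
- longest: 7 + 21 + 84 = day 112;
- at mean width: 5 + 15 + 56 = day 76, to 7 + 15 + 84 = day 106.

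| Visit | Approximate day | Distractor present in group A |
|---|---|---|
| Immediately after surgery | 0 | yes, all |
| 1 month | 30 | yes, all |
| 3 months | 91 | possibly, in some (71 to 112 spans 91) |
| 6 and 12 months | 182 and 365 | not implied by the schedule |

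An examiner who palpates the segment or measures the gap in the mouth at the first two visits can see or feel the appliance. In group B the same holds for as long as the splint is in place, which is not stated. No plate removal is described either, so later scans may show plates in group B only.

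**Step 3: would masking hardware be enough?** Distraction starts only after 5 to 7 days, whereas the group B segment is repositioned at surgery. On the immediate scan the gap itself may therefore indicate the group, whatever is masked. Distraction would end between 5 + 10 = day 15 and 7 + 21 = day 28, before the 1-month visit. This particular cue is then confined to the immediate scan.

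**Step 4: blinding and selection bias.** Allocation rests on the surgeon's judgement of morphology, width, bone stock, soft tissue and expected compliance (Postoperative Care). Evaluator blinding acts after allocation, so it cannot reduce bias that arises there.

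**The case against.** The strongest reply is that much of the detail needed to judge blinding could sit in a full protocol that is not shown: field of view, image preparation, who examines and when hardware is removed. That silence is no fault in an article. This stands, and it limits the point to what the article itself states, namely the re-read rule, the palpation, the clinical gap measurement and the claim covering all assessments.

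Several stronger readings are tempting but not supported:

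- A reader might infer that practically every postoperative assessment is unblinded. The article does not show this. Preoperative assessments are unaffected, in-mouth examination at 6 and 12 months could be blinded if the hardware is out and the examiner is independent, and arch form is also read from dental models, which need not show plates.
- A reader might infer that Landry healing scores are unblinded because they are given at the chairside. The article says only that "Soft tissue healing will be evaluated by blinded assessors using the Landry wound healing scale". It does not say whether scoring is in the mouth or from photographs.
- A reader might try to put a number on the bias. No figure in the document supports a size or a direction. The Discussion says only that distraction may close wide gaps more predictably, and it credits Le Fort I with a possible advantage in facial projection.
- A reader might conclude that all images should be cropped to the gap. That would make arch form, a primary outcome, unreadable on occlusal views and would impair the CBCT part of the stability grade.

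Control of selection bias also does not rest on blinding alone. Postoperative Care adds baseline comparison, regression, stratified enrolment and propensity score adjustment. The error there is one of attribution within a sentence, and it is easily corrected.

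**Conclusion.** The point holds in a limited form. The re-read rule cannot restore blinding, because the second reviewer sees the same hardware. This follows from the article's wording and needs no assumption. The statement that all assessments are blinded also fails for palpation and for the clinical part of gap closure while a distractor or splint is in the mouth. In group A this means immediately after surgery and at 1 month, and possibly at 3 months, provided the distractor stays through consolidation and distraction distance equals cleft width. The position at 6 and 12 months cannot be settled from the document. The size of any bias is not derivable.

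This should be corrected, because a stated design property does not hold and the correction is cheap. It does not invalidate the study, and it does not show that every scan or every healing score is compromised.

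**What to change.** 1. For the CBCT gap measurement only, have existing staff crop or mask images to exclude hardware where feasible, before coding.
2. Have the two planned evaluators read every scan, and analyse the mean of their two readings.
3. Delete the conditional re-read rule from both sections. In its place, record and report which readings were unblinded.
4. Do not crop images used for arch form or segment stability. Read arch form from coded dental models where possible.
5. Limit the blinding statement: report palpation and any other in-mouth grade as unblinded while appliances are present, and treat the masked CBCT measure as the main evidence on gap closure.
6. In Postoperative Care, remove evaluator blinding from the sentence on selection bias and describe it as protection against detection bias.

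The cost is some image preparation and a less favourable blinding statement. Masked images may still carry cues, notably the immediate postoperative scan, and the record in item 3 would show how often. No change to treatment or visits is needed.

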### Preoperative Assessment

All patients will undergo clinical examination and medical history review. Informed consent will be obtained. The interdental cleft width will be measured using Castroviejo calipers, and arch form will be classified. CBCT, lateral cephalograms, and maxillary occlusal radiographs will be performed to assess the cleft.

### The Dentoalveolar Transport Distraction Group

Orthodontic spacing will be created between the premolars. A horizontal mucosal incision will be made, followed by horizontal, anterior, posterior, and interdental osteotomies. A custom-made intraoral distractor will be fixed. After a 5- to 7-day latency period, distraction will begin at 1 mm per day until cleft closure. A consolidation period of 8 to 12 weeks will follow.

### The Unilateral Le Fort I Advancement Group

Orthodontic preparation will be done similarly. A horizontal incision will be made, and a mucoperiosteal flap will be raised to expose the anatomical landmarks. Standard Le Fort I and palatal osteotomies will be carried out. The segment will be medially repositioned and fixed using a surgical splint and bone plates. The flap will be closed with 3‐0 Vicryl sutures.

### Postoperative Care

All patients will receive antibiotics, analgesics, chlorhexidine mouth rinses, and dietary instructions. Follow-up visits will be scheduled at 1 month, 3 months, 6 months, and 1 year postoperatively.

As this is a prospective observational study, treatment allocation is not randomized. Patients are assigned to either the dentoalveolar transport distraction group or the unilateral Le Fort I advancement group based on specific clinical indications determined by the treating maxillofacial surgeon. Criteria such as cleft morphology, cleft width, presence of adequate bone stock for distraction, soft tissue quality, and anticipated compliance with the distraction protocols are considered during group assignment. To minimize selection bias, all assessments are conducted using standardized protocols, and outcome evaluators are blinded to the intervention type. Additionally, baseline characteristics of both groups will be statistically compared to assess equivalency, and any confounders will be adjusted for during analysis using multivariate regression techniques.

To further minimize allocation bias inherent to the nonrandomized design, we will perform stratified enrollment based on cleft width and age groups. Additionally, a propensity score adjustment will be conducted in the final analysis to balance any observed confounders between groups.

Missing data may arise from loss to follow-up or incomplete clinical or radiographic records. These will be assessed for randomness using the Little missing completely at random test. If data are missing at random, multiple imputation using chained equations will be applied to minimize bias. Variables with >20% missing data will be excluded from the primary analysis but may be used in sensitivity analysis. Potential confounders, such as patient age, cleft width at baseline, and compliance with treatment protocols, will be identified a priori based on clinical relevance and literature review. These variables will be included in multivariate regression models (eg, linear regression for continuous outcomes such as gap width and logistic regression for binary outcomes such as successful closure) to adjust the primary effect estimates. Adjusted effect sizes and CIs will be reported alongside unadjusted comparisons.

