### Primary Outcome

The primary outcomes evaluated in this study will be as follows:

Closure of the alveolar gap: measured clinically and radiographically (ie, CBCT) at 5 time points: preoperatively; immediately after surgery; and at 1, 3, and 6 months and 1 year of follow-upArch form: classified (U-shaped, V-shaped, or asymmetrical) via models and radiographs at each follow-up

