### Statistical Analysis

All data will be analyzed using RStudio (version 4.3.2; Posit, PBC). Continuous variables (eg, cleft width and bone segment stability score) will be tested for normality using the Shapiro-Wilk test. Depending on data distribution, between-group comparisons will be performed using either the unpaired *t* test (for normally distributed data) or the Mann-Whitney *U* test (for nonparametric data). Categorical outcomes, such as arch form classification (U-shaped, V-shaped, or asymmetrical) and wound healing grades (from the Landry wound healing scale), will be compared using the chi-square test or Fisher exact test, as appropriate.

Longitudinal outcomes (eg, segment stability across time points) will be analyzed using repeated measures ANOVA for normally distributed data or generalized estimating equations for nonparametric repeated measures. All outcome measures will be reported with 95% CIs, and *P*<.05 will be considered statistically significant. Missing data will be handled using multiple imputation, and any potential confounders, such as age or initial cleft width, will be adjusted for using multivariate regression analysis.

To assess the robustness of results, sensitivity analysis will be conducted by comparing results from multiple imputation with complete-case analysis and worst-case scenario imputation.

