## Results

As of June 2025, patient recruitment, which began in April 2023, is ongoing. Out of 14 intended participants, 12 (85%) have been enrolled (with 7 in the dentoalveolar transport distraction group and 5 in the unilateral Le Fort I advancement group). The enrolled cohort includes 8 male individuals and 4 female individuals, with a mean age of 16.8 (SD 3.9; range 10-23) years. The average cleft width among the participants was 1.5 (SD 0.34; range 1.0-2.1) cm.

Data collection is anticipated to conclude by December 2025, and the results are expected to be published in 2026.

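### The 20% missing-data exclusion does not exempt primary outcomes, and the Statistical Analysis section imputes without that limit, so the two sections part ways once more than 20% is missing

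*Protocol article*

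**What the plan says.** The protocol article deals with missing data in two places.

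**Postoperative Care** gives the longer account. It names where gaps will come from: "Missing data may arise from loss to follow-up or incomplete clinical or radiographic records". It plans Little's test, then a conditional imputation: "If data are missing at random, multiple imputation using chained equations will be applied to minimize bias". It then sets a limit: "Variables with >20% missing data will be excluded from the primary analysis but may be used in sensitivity analysis". The sentences after that turn to confounders and regression adjustment.

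**Statistical Analysis** gives a shorter account: "Missing data will be handled using multiple imputation". It carries neither the 20% limit nor the missing-at-random condition, and it does not point back to Postoperative Care. It also promises that "sensitivity analysis will be conducted by comparing results from multiple imputation with complete-case analysis and worst-case scenario imputation".

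The outcomes that could be affected are listed under Primary Outcome. One is gap closure ("Closure of the alveolar gap: measured clinically and radiographically"); the other is arch form, classified at each follow-up. The planned sample is 14, with 7 per group. The Results section reports the position in June 2025: "Out of 14 intended participants, 12 (85%) have been enrolled", 7 in the distraction group and 5 in the Le Fort I group.

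**The concern.** A rule that removes a variable because of how much of it is missing is tolerable for an optional covariate. Applied to a primary outcome, it lets the data decide which primary comparisons are reported. As written, the rule covers variables in general. Its paragraph opens with loss to follow-up and incomplete radiographic records, which affect follow-up scans and arch-form classifications rather than baseline age or cleft width.

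Above 20% missing, an analyst working from Postoperative Care would move the outcome to sensitivity analysis at most. An analyst working from Statistical Analysis would impute it and keep it as primary. From the same data the two could report different sets of primary results, and a choice made after seeing the data would be open to the charge of selection. In a study this small, the difference can turn on one missed scan.

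**Working it through.** **Inputs from the protocol article.** Limit: more than 20% missing. Planned N = 14 (7 per group). Enrolled by June 2025: N = 12 (7 and 5). Assessments: six (preoperative, immediately postoperative, and 1, 3, 6 and 12 months), of which four are scheduled follow-ups. No expected dropout rate is given, and the unit for the 20% is not stated.

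**The plan's own figure.** The sample-size formula with the stated values gives (1.64 + 0.84)² × (0.94 × 0.06 + 0.44 × 0.56) / 0.50² = 6.1504 × 0.3028 / 0.25 = 7.45 per group, which the article reports as 7, hence 14. That figure serves here only as a denominator.

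**Step 1: share missing at one visit, whole sample.** Share = m / N, excluded if above 20%.

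| N | m = 2 | m = 3 |
|---|---|---|
| 12 | 16.7%, kept | 25.0%, excluded |
| 13 | 15.4%, kept | 23.1%, excluded |
| 14 | 14.3%, kept | 21.4%, excluded |

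On this count, the third missing patient crosses the limit at every sample size from 12 to 14.

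**Step 2: other ways of counting.**
- Within a group at one visit: 1/7 = 14.3% and 1/5 = 20.0% are not above 20%; 2/7 = 28.6% and 2/5 = 40.0% are. Two patients suffice.
- Over all six assessments, with 3 patients missing all four scheduled follow-ups: 3 × 4 = 12 missing values. 12/(14 × 6) = 12/84 = 14.3%, and 12/(12 × 6) = 12/72 = 16.7%. The outcome is kept.
- Over the four follow-ups only: 12/(14 × 4) = 12/56 = 21.4%, and 12/(12 × 4) = 12/48 = 25.0%. The outcome is excluded.

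The same loss of patients therefore keeps or removes the outcome depending on a unit that the text does not fix.

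**Step 3: chance of reaching 3 missing at a given visit.** The per-visit missingness p is assumed, and patients are taken as independent: P(X ≥ 3) = 1 − P(0) − P(1) − P(2), with X binomial(N, p). For N = 14 and p = 0.10 this is 1 − 0.229 − 0.356 − 0.257 = 0.158.

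| Assumed p | N = 14 | N = 12 |
|---|---|---|
| 5% | 3% | 2% |
| 10% | 16% | 11% |
| 15% | 35% | 26% |
| 20% | 55% | 44% |

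These figures are for a single visit, counted over the whole sample. They illustrate sensitivity to p and are not forecasts.

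**The case against.** The strongest reply is that there is no conflict. Postoperative Care gives the procedure, and Statistical Analysis condenses it to one clause, in a sentence that also condenses the confounder plan. On that view both can be followed: impute up to 20%, exclude beyond it. This reading is possible. A reader might infer that the Statistical Analysis section promises to impute *all* missing data and so flatly contradicts the limit; it does not use that word, and the inference goes too far. What stands is that the section states imputation without qualification and does not refer to the limit.

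Second, the rule may have been meant for covariates, since the following sentences concern confounders. That is plausible. However, confounders are introduced only after the rule, no exemption for outcomes is given, and the paragraph starts from losses that fall on follow-up outcomes. If covariates were meant, the text should say so.

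Third, no dropouts or major protocol deviations had been recorded by June 2025, and at 5% missingness the chance of crossing the limit is small. This is fair, and it is why the range above starts at 5%. It does not rule out single missed scans or incomplete records.

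Fourth, a cap on imputation is defensible in groups of 7 and 5, where imputed results lean on the model. That is a reason to report such a result with caution. It does not justify letting the observed missingness decide whether a primary outcome is primary. Permitting the excluded variable in sensitivity analysis does not return it to the primary analysis.

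Finally, an article may leave detail to a fuller document. Here, though, the exclusion rule is printed, and the point is what it does as printed.

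**Conclusion.** The point holds as a defect of scope and consistency. A printed exclusion rule, followed literally, can take a primary outcome out of the primary analysis because of the amount of missing data, and the Statistical Analysis section does not carry the same limit. The sections diverge only above 20% missing.

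The size depends on two things the article does not give: the counting unit and the missingness rate. Three patients is the trigger only if the share is counted per visit over the whole sample, and the loss is then of that outcome at that visit.

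Two stronger readings are not supported. One is that three missing patients would delete a primary outcome outright: over all six assessments, three patients missing every scheduled follow-up leave it in. The other is that the outcomes dropped would be those where failures concentrate. Loss related to treatment failure is possible, but nothing in the article shows it, and the planned worst-case analysis partly addresses it. Nor has the rule been shown to have come into play, since no dropouts were recorded by June 2025.

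**What to change.** In Postoperative Care, limit the 20% exclusion to optional covariates. In both Postoperative Care and Statistical Analysis, state the same rule: gap closure and arch form stay in the primary analysis under multiple imputation, and the fraction missing is reported by group and visit. Keep the complete-case and worst-case analyses already planned as the sensitivity set. If the limit is retained for covariates, state how the 20% is counted. Make the change before data lock.

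The cost is a few sentences. The small downside is that an outcome with much missing data will be reported with a wide interval that depends more on the imputation model; reporting the fraction missing beside it lets readers judge how far to rely on it.

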### Sample Size Calculation

The minimum required sample size was calculated using the standard formula for comparing 2 independent means, as shown below:

$$N=\frac{{\left(Z_{\alpha }+Z_{\beta }\right)}^{2}\left(P_{1}\left(1-P_{1}\right)+P_{2}\left(1-P_{2}\right)\;\right)}{{\left(P2-P1\right)}^{2}}$$

$$Z_{\alpha }=1.64$$

α= Type I error at 5%

$$Z_{\beta }=0.84$$

β= Type II error at 20%

The following parameters were used for the sample size calculation:

Improved facial esthetic and balance in maxillary DO=94%Improved facial esthetic and balance in maxillary unilateral Le Fort 1 osteotomy=44% (estimated clinically significant difference=50%)Difference (P2−P1)=50%Minimum sample size N=2×(1.64+0.84)^2^ (0.94) (1‐0.94) + 0.44(1‐0.44)/(0.50)^2^=7 each in 2 groupsSample size=14, with 7 in each group

Using a 2-sided z test with *α*=.05 and power of 80%, assuming a success rate of 94% in the dentoalveolar transport distraction group and 44% in the unilateral Le Fort I advancement group, the required sample size is 7 per group (N=14). This includes a 50% absolute effect size and accounts for variability in response.

The 50% effect size estimate was based on the internal pilot data and clinical observations. However, we acknowledge the possibility of overestimation. A sensitivity analysis will also consider a 40% effect size, which would require a larger sample and will be addressed in future studies.

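### The adjustment plan names compliance, observed after treatment starts, as a confounder, and promises logistic and propensity models that 12 to 14 patients can barely support

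*Protocol article*

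**What the plan says.** All the relevant text is in the protocol article.

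- **Allocation.** Treatment is not randomized. Under Postoperative Care, the surgeon weighs cleft morphology and cleft width, and then "presence of adequate bone stock for distraction, soft tissue quality, and anticipated compliance with the distraction protocols are considered during group assignment". The Overview gives a shorter list: morphology, bone stock and expected compliance.
- **Covariates.** Postoperative Care states "Potential confounders, such as patient age, cleft width at baseline, and compliance with treatment protocols, will be identified a priori based on clinical relevance", and that these variables go into the regression models which adjust the primary effect estimates. The Statistical Analysis section gives age and initial cleft width as its examples and does not mention compliance.
- **Compliance.** Feasibility and Acceptability treats compliance with the distraction protocol as something followed during the study.
- **Models.** Linear regression is named for gap width and "logistic regression for binary outcomes such as successful closure". In addition, "a propensity score adjustment will be conducted in the final analysis to balance any observed confounders between groups".
- **Baseline.** The plan says that "baseline characteristics of both groups will be statistically compared to assess equivalency".
- **Size.** 14 patients are planned (7 per group). As of June 2025, 12 were enrolled: 7 for distraction and 5 for Le Fort I.

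**The concern.** A confounder precedes treatment and influences both the choice of treatment and the outcome. Observed compliance comes after the choice. For the distraction component it is part of how that treatment works or fails, and it has no counterpart in group B. A model that holds it fixed no longer estimates the difference between the two techniques as delivered.

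The second issue is capacity. A logistic model needs successes and failures in both groups before it can return a finite odds ratio. A propensity model needs enough patients per covariate for the groups not to be perfectly predicted. With 5 to 7 patients in the smaller group, both conditions are doubtful.

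Third, a non-significant baseline test in groups of this size would be read as evidence that the groups are alike, which it is not.

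This matters because the Discussion offers multivariate regression as the answer to non-random allocation, and the Conclusions in the abstract hope to guide the choice of technique.

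**Working it through.** **1. Compliance: the sections side by side.** Postoperative Care speaks of anticipated compliance when it describes allocation, and of compliance with treatment protocols when it lists covariates. Feasibility and Acceptability has compliance tracked as treatment proceeds. Read together, the covariate is the observed quantity. Daily distraction after a latency period belongs to group A only (Intervention Delivery). The direction and size of the resulting bias cannot be computed, because the article gives no compliance or gap data by group.

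**2. The plan's own planning figure.** The rates come from Sample Size Calculation: 94% for distraction and 44% for Le Fort I. The printed formula gives (1.64 + 0.84)² × (0.94×0.06 + 0.44×0.56) / 0.50² = 6.1504 × 0.3028 / 0.25 = 7.45, reported as 7 per group. The value 1.64 is one-sided although the text describes a two-sided test; that is a separate matter. The rates refer to improved facial esthetics, and the article gives no closure rate, so their use below is an assumption.

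**3. Logistic regression with treatment alone.** The maximum likelihood odds ratio is not finite when either group is all successes or all failures.

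- Group A at 94%: 0.94⁷ = 0.648; 0.06⁷ is negligible.
- Group B at 44%, n = 7: 0.44⁷ + 0.56⁷ = 0.0032 + 0.0173 = 0.0205.
- Group B at 44%, n = 5: 0.44⁵ + 0.56⁵ = 0.0165 + 0.0551 = 0.0716.
- 7+7: 1 − (1 − 0.648)(1 − 0.0205) = 0.66.
- 7+5: 1 − (1 − 0.648)(1 − 0.0716) = 0.67.

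With an assumed 75% in group A, 0.75⁷ + 0.25⁷ = 0.1335:

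- 7+7: 1 − (0.8665)(0.9795) = 0.15.
- 7+5: 1 − (0.8665)(0.9284) = 0.20.

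**4. Adding covariates.** These figures come from simulation (1,500 data sets per setting, independent normal covariates with no effect on outcome, separation checked by linear programming).

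| Covariates besides treatment | 94%/44%, 7+7 | 94%/44%, 7+5 | 75%/44%, 7+7 | 75%/44%, 7+5 |
|---|---|---|---|---|
| 2 | 0.69 | 0.73 | 0.18 | 0.27 |
| 3 | 0.73 | 0.82 | 0.29 | 0.45 |

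At the planning rates the expected number of failures is 7×0.06 + 7×0.56 = 4.3 (7+7) or 7×0.06 + 5×0.56 = 3.2 (7+5). That is about one per parameter in a model with treatment and three covariates.

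**5. Propensity score.** Postoperative Care names five allocation criteria. Five covariates leave 7/5 = 1.4 patients per covariate in the smaller group at 7+7, and 5/5 = 1.0 at 7+5. The simulated chance (1,000 data sets per setting) that the model separates the groups perfectly is:

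| Shift between groups per covariate (assumption) | 7+7 | 7+5 |
|---|---|---|
| none | 0.23 | 0.43 |
| 0.5 SD | 0.50 | 0.69 |
| 1 SD | 0.90 | 0.94 |

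With only two covariates the range is 0.002–0.14 (7+7) and 0.02–0.24 (7+5). The difficulty therefore grows as the model takes in the real reasons for allocation.

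**6. Linear model for gap width.** An intercept, treatment and three covariates leave 14 − 5 = 9 or 12 − 5 = 7 residual degrees of freedom. Treatment and cleft width alone leave 14 − 3 = 11 or 12 − 3 = 9. It can be fitted, but with little room.

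**7. Baseline tests.** A two-sided 5% t test has 80% power only for a difference of 1.63 SD (7+7) or 1.82 SD (7+5). Smaller imbalances that could matter would usually go undetected.

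**The case against.** A reader might infer that every adjusted effect will be biased or undefined. The documents do not support that. Gap closure is a primary outcome measured radiographically, its linear model can be fitted, and unadjusted comparisons are to be reported alongside. Logistic regression is given as an example, for a binary closure outcome that the outcome sections do not define. The high separation figures rest on a borrowed facial-esthetic rate and fall sharply at 75%. All of this stands and limits the claim about undefined estimates to the logistic and propensity models.

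A reader might also infer that the plan excludes most of the allocation criteria. It does not: both covariate lists are illustrative, and the text promises to adjust for any confounders. That is fair, but it does not resolve the difficulty. Leaving the criteria out leaves confounding by indication, and putting them in makes the models harder to estimate. Nor can one conclude that the groups have no overlap on bone stock, since the text says only that it is considered.

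Compliance could be meant as the baseline expectation, because the Overview uses similar words for an allocation criterion and the covariates are to be chosen in advance. That reading is possible, but the text does not say so. No dropouts or major deviations were recorded up to June 2025, so observed compliance may vary little and the resulting bias may be small. Finally, the Discussion already admits the small sample and the non-random allocation, but it then points to regression as the remedy.

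**Conclusion.** The point holds in limited form. As written, the plan adjusts for a variable observed after treatment starts, and its two covariate lists differ. This error does not depend on any rate or sample size, though its numerical effect is unknown.

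The logistic and propensity models are poorly matched to 12–14 patients. With treatment alone, the chance of no finite odds ratio is about 66% if closure is near 94%/44%, and 15–20% if group A is at 75%; both rate pairs are assumptions. Covariates raise it to 69–82% and 18–45% respectively. An undefined result is therefore a serious risk, not a certainty, and it does not extend to the linear model. Baseline significance tests cannot establish equivalency at this size. No analysis available here removes confounding by indication, and that includes the smaller model proposed below.

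**What to change.** 1. Remove observed compliance from all adjustment models and report it descriptively. If anticipated compliance at baseline was meant, say so. Make the covariate lists in Postoperative Care and Statistical Analysis agree.
2. Prespecify one minimal linear model: gap width on treatment and baseline cleft width, with age added in a sensitivity model.
3. For binary closure, use Firth-penalised or exact logistic regression.
4. Drop the propensity score, or label it exploratory.
5. Replace tests of baseline equivalency with a table of standardized differences, including the surgeon's allocation criteria where they were recorded.
6. State that confounding by indication remains and that results are associations under surgeon-selected treatment.

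The cost is mainly analysis wording, to be settled before the final analysis. With 12 of 14 patients already enrolled, some allocation criteria may not be recoverable, hence the condition in item 5. The price is fewer covariates and a weaker causal claim.
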